#### Measures

Table 1 provides an overview of the measurement instruments used. These instruments were chosen according to their comparability in national and international mental health research, and their psychometric characteristics. Duration and sensitivity to measure change were also taken into consideration. The first author as well as trained interviewers will carry out the interviews, which will take place on a location preferred by the client, at home or at team location. The interviewers were trained by explaining the topic list and using role-play, in order minimize bias due to inter-reviewer differences. Moreover, the first one or two interviews will be performed in dyads, with the researcher. Data will be entered into a secured database by researchers or research assistants. Participants’ names will be changed into randomly assigned numbers of which only two of the authors have the key.

**Table 1 Tab1:** Overview of measurement instruments

Concept	Instrument	Level	T0	T1	T2^a^
Primary outcome measures					
Societal participation	Birchwood Social Functioning Scale (SFS)	Client	x	x	x
Criminal victimization	The Safety Monitor, section 4	Client	x	x	x
Discrimination and stigmatization	Discrimination and Stigma Scale (DISC-12)	Client	x	x	x
Perceived safety	The Safety Monitor, section 3	Client	x	x	x
Secondary outcome measures					
Acknowledgement of adversities	Structured questionnaire on feelings when discussing adversities	Client	x	x	x
Knowledge on rehabilitation and adversities	Structured questionnaire	MHP	x	x	x
Self-efficacy	Mental Health Confidence Scale (MHCS)	Client	x	x	x
Quality of Life	Manchester Short Assessment of Quality of Life (MANSA)	Client	x	x	x
General psycho-social functioning	The Health of the Nation Outcome Scales (HoNOS)	MHP	x	x	x
Additional and control measures					
Socio-demographic characteristics	Structured questionnaire	Client	x	x	x
Primary diagnosis	Structured questionnaire	MHP	x		
Number of years in MHC	Structured questionnaire	Client	x		
Social Support	Inventory of Social Reliance	Client	x	x	x
Neighborhood nuisance	The Safety Monitor, section 1 and 2	Client	x	x	x
Perpetration	The Safety Monitor, section 5	Client	x	x	x
FACT fidelity	CCAF scores	Team	x		x
Adherence to rehabilitation principles	Treatment plan (sample of 15% per team)	Client	x		x

^a^*T0* baseline, *T1* 9 months follow-up, *T2* 18 months follow-up

#### Primary outcome measures cluster RCT

The first primary outcome measure is *social participation *measured with the Birchwood Social Functioning Scale (SFS) [44]. It measures social functioning on seven domains: social engagement/withdrawal, interpersonal behavior, pro-social activities, recreation, independence-competence, independence-performance, and employment/occupation. The SFS is a reliable, valid, sensitive to change, instrument with a high internal consistency (α = 0.80) [44].

The second primary outcome measure is victimization related to societal participation and includes the following:2.*Criminal victimization* will be measured with the Dutch version of the Safety Monitor, developed by the Dutch Ministry of Security and Justice [45], and strongly resembles the International Crime Victimization Survey [46]. It is a self-report questionnaire in which section 4 measures victimization on 15 crimes: burglary, theft from car, car theft, theft of other motorized vehicles, bicycle theft, (attempt to) robbery, theft (other than previously categorized), sexual intimidation or assault, threats (of violence), physical assault, vandalism, identity fraud, fraud with buying/selling items/services, hacking, cyber bullying. For each incident reported in the past 12 months, participants are asked to give more information about the incident.3.*Perceived safety* will also be measured with the Safety Monitor. The participant is asked whether they ever feel unsafe (yes/no) and how often (often/sometimes/rarely).4.*Discrimination and stigmatization* is assessed by the Discrimination and Stigmatization Scale (DISC-12) [47]. This scale consists of four subscales: unfair treatment, stopping self, overcoming stigma, positive treatment. The DISC-12 contains 32 items answered on a 4-point scale ranging from ‘no difference (0)’ to ‘a lot (3)’. A ‘not applicable’ answer is available when the participant was not involved in the described situation. Psychometric properties are considered good, Cronbach’s alpha is 0.78 and the inter-rater reliability ranges from 0.62 to 0.95.

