## Background

In most western countries, deinstitutionalization has led to an increase of community-based care with a focus on promoting the recovery and societal integration of people with severe mental illness (SMI) [1]. To achieve successful integration into community life, psychiatric rehabilitation methods were developed in order to support people with SMI to regain a meaningful life and valued social roles [2, 3]. Within the field of psychiatric rehabilitation, several evidence-based practices can be identified. The Boston Approach to Psychiatric Rehabilitation (BPR) has proven to be effective in promoting new perspectives, role functioning, and life satisfaction [4, 5]. Another evidence-based rehabilitation intervention is the Individual Placement and Support (IPS) model of supported employment [6]. Employment specialists successfully support clients to search for and get a job, and also coach clients about working situations in order to maintain employment.

There are still substantial challenges to work on in community-based care, especially concerning supporting clients in their social and community participation. A lack of support in these areas may lead to unemployment, poverty, social isolation and even imprisonment [7]. Studies have also shown that these negative consequences may lead to an increase of victimization rates [8–10]. Not only are people with SMI more likely to experience victimization than other community members, in contrast to popular public belief, they are also more likely to become a victim of a crime rather than being the perpetrator [11–15]. Prevalence rates of violent victimization among persons with SMI range between 7 and 56% in the previous year – 11 times greater than the general population [8]. A recent nationwide study in the Netherlands examined prevalence rates of several types of victimization and found that almost 20% of people with SMI were a victim of serious crimes in the previous year, such as sexual harassment/assault, violence, and physical assault [11]. In most cases, the victim knew the perpetrators of these crimes.

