## Methods

### Design

This study includes: 1) a process evaluation and 2) a two-armed multi center cluster randomized controlled trial (RCT) to follow the implementation process and determine the effectiveness of the Victoria intervention. Participants include adult clients of eight F-ACT teams who are interviewed about their victimization experiences and rehabilitation process at three points in time: at baseline, and after 9 and 18 months. Study characteristics are described according to SPIRIT guidelines [37]. This study was approved by the Medical Ethical Committee of the Elisabeth Hospital in Tilburg (NL53845.028.15) on the 18th of November 2015 for all participating sites. The study is registered with the Dutch Trial Register (NTR 5585).

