### RCT analyses

#### Sample size

Sample size is calculated using the model of Twisk [56]. This model is suitable for multiple measurements over time, but can also be used for cluster randomization. With the ratio of the number of subjects in the compared groups being 1 (*r*), a correlation coefficient of the repeated measurements of 0.20 (ρ), a conservative difference between the groups in the mean value of social functioning of 0.25 (*v*), and a power of 1-β = 0.80, the number of participants needed is 151 for each condition at T2 measurement (α = 0.05, two-tailed). Taking into account an attrition rate of 15% for loss due to follow-up or consent withdrawal, 173 participants per condition need to be recruited to achieve the required power.$$ N=\frac{Z\left(1-\alpha /2\right)+Z\left(1-\beta \right)\ 2\ \sigma 2\left(r+1\right)\left[1+\left(T-1\right)\rho \right]}{v2r\ T} $$

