#### Statistical analyses

Data will be analyzed according to the ‘intention to treat’ principle, meaning that F-ACT teams (and thus clients) that are assigned to either experimental or control condition in randomization, will be analyzed accordingly. Because of the cluster design and multiple measurements over time, generalized linear mixed models (GLMM) will be used with SPSS (version 22); depending on the distribution of the outcome variable a logistic regression model or a linear regression model will be adopted. GLMM is robust with respect to missing data [57], which is not uncommon in research among outpatients with SMI. Therefore, multiple imputation is not necessary. To analyze the effect of the Victoria intervention on the main outcomes, differences in societal participation and victimization, both conditions will be compared after 9 and 18 months follow-up with time as a categorical variable. Measurements over time are nested within participants; therefore, random slopes will be added for time. Random intercepts will be added for the participants. The same procedure will be adopted for secondary outcome measures. Furthermore, possible confounders will be examined, such as socio-demographic characteristics, current diagnosis, number of years in MHC, or perpetration on whether they need to be added to the model. Only significant confounders will be added to the final model. In all analyses performed, two-tailed *p*-values < 0.05 are considered significant. Finally, Akaike’s Information Criterion (AIC) will be used for the selection of the final model that fits the data best and is the most generalizable [58].

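### A 12-month recall of criminal victimization at interviews 9 months apart puts pre-baseline months into the 9-month comparison, diluting it, and makes successive visits share incidents

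*Protocol article*

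**What the plan says.** Table 1 of the Protocol article (Measures) lists criminal victimization among the primary outcome measures, taken with "The Safety Monitor, section 4" at T0, T1 and T2. Its footnote defines T1 as "9 months follow-up" and T2 as the 18-month interview. Under Primary outcome measures cluster RCT, it is one component of the second primary outcome and covers 15 crimes. The only reference period given there is 12 months: "For each incident reported in the past 12 months, participants are asked to give more information about the incident".

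The Design section sets the interviews "at three points in time: at baseline, and after 9 and 18 months". Under Statistical analyses, "both conditions will be compared after 9 and 18 months follow-up with time as a categorical variable". The model has random intercepts for participants and random slopes for time.

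The article gives no shorter recall period for T1 or T2. It also states no rule for incidents that predate baseline or were reported at the previous interview.

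**The concern.** The recall period is three months longer than the gap between interviews, with two consequences.

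First, part of what is counted at T1 happened before the trial started. The intervention cannot change those incidents, so in expectation they add equally to both arms and pull the 9-month contrast towards no difference. A real early effect could be read as none.

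Second, neighbouring interviews ask about some of the same months. An incident just before baseline can be reported at T0 and T1, and one between months 6 and 9 at T1 and T2. This creates correlation between successive visits that comes from the questionnaire rather than from the clients, and it blurs the course over time that the model is meant to describe.

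**Working it through.** **Inputs.** Recall 12 months (Primary outcome measures cluster RCT); interviews at months 0, 9 and 18 (Design; Table 1); two-sided alpha 0.05 and "a power of 1-β = 0.80" (Sample size).

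**The plan's own figure.** The only sample-size figure stated is 151 per condition, and it is for social functioning. Take the repeated-measures formula with sigma = 1 (assumed, since it is not stated), two follow-up measurements, correlation 0.20 and difference 0.25. Then (1.96 + 0.842)² × 2 × (1 + 0.20) / (0.25² × 2) = 150.7, that is 151. The figure reproduces, but it says nothing about victimization.

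**Windows, in months from baseline** (interview time minus 12, up to interview time):

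- T0: -12 to 0
- T1: -3 to 9
- T2: 6 to 18

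T0 and T1 share months -3 to 0, so 3/12 = 25% of the T1 window is pre-baseline. T1 and T2 share months 6 to 9, which is 25% of each. T0 and T2 do not overlap, and T2 contains no pre-baseline time.

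**Dilution at T1.** Assume a constant monthly rate λ in controls, the same rate in both arms before baseline, and rate Rλ in the intervention arm from baseline on. Expected incidents in the T1 window are 12λ in controls and (3 + 9R)λ in the intervention arm. The observed rate ratio is (3 + 9R)/12 = 0.25 + 0.75R. Thus 0.50 becomes 0.625, 0.70 becomes 0.775 and 0.80 becomes 0.85.

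**Cost in clients.** The attainable alternative at month 9 is a 9-month window, 0 to 9. It removes the dilution but also holds fewer events, so both effects must be counted. With yearly control risk p, λ = -ln(1 - p)/12. The proportions with at least one incident are:

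- current window: p v 1 - exp[-λ(3 + 9R)]
- clean window: 1 - exp(-9λ) v 1 - exp(-9λR)

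Worked example, p = 0.20 and R = 0.70: λ = 0.0186. The current window gives 20.0% v 15.9%; the clean window gives 15.4% v 11.1%. The usual two-proportion formula (pooled variance under the null, alpha 0.05 two-sided, power 0.80) gives 1,361 and 949 per arm, and 1361/949 = 1.43.

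| p (assumed) | R (assumed) | Current T1 window | n per arm | Clean 9-month window | n per arm | Ratio |
|---|---|---|---|---|---|---|
| 20% | 0.5 | 20.0% v 13.0% | 443 | 15.4% v 8.0% | 297 | 1.49 |
| 20% | 0.6 | 20.0% v 14.5% | 729 | 15.4% v 9.6% | 499 | 1.46 |
| 20% | 0.7 | 20.0% v 15.9% | 1361 | 15.4% v 11.1% | 949 | 1.43 |
| 20% | 0.8 | 20.0% v 17.3% | 3210 | 15.4% v 12.5% | 2275 | 1.41 |
| 40% | 0.5 | 40.0% v 27.3% | 218 | 31.8% v 17.4% | 140 | 1.56 |
| 40% | 0.6 | 40.0% v 30.1% | 361 | 31.8% v 20.5% | 237 | 1.52 |
| 40% | 0.7 | 40.0% v 32.7% | 679 | 31.8% v 23.5% | 455 | 1.49 |
| 40% | 0.8 | 40.0% v 35.2% | 1613 | 31.8% v 26.4% | 1098 | 1.47 |

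The ratio runs from 1.41 to 1.56. These counts ignore clustering and are only a way to compare the two windows; they are not a sample size for this trial.

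**The case against.** The best defence is that the damage is narrow. The 18-month window is entirely post-baseline, and the sample size is stated for that visit. Both arms answer the same question, so the pre-baseline months do not by themselves favour one arm. There is also a reason for a 12-month period: the Measures section says instruments were chosen partly for comparability with other research. Finally, the follow-up questions on each incident may already ask for its date, and a condensed article need not list them. All of this stands, and it limits the point to the 9-month comparison and the course over time. It does not remove it: the article fixes the 12-month period, the 9-month spacing and a comparison at 9 months, and together these produce a diluted contrast.

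Several stronger readings are tempting but not supported:

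- *The sample-size penalty is nearly twofold.* For p = 20% and R = 0.7, a 12-month window wholly after baseline would need 729 per arm, and 1361/729 = 1.87. No such window can exist at month 9.
- *The 20% rate is the plan's own rate for this outcome.* The Background says "almost 20% of people with SMI were a victim of serious crimes in the previous year". The outcome here covers 15 crimes, including bicycle theft, vandalism and hacking, and its rate is not given.
- *Events are counted twice.* No total is summed over visits; each visit has its own 12-month status.
- *The visits are analysed as if unrelated.* Measurements are nested within participants, so within-person correlation is modelled. What remains is an artefactual share of that correlation between adjacent visits.
- *Even more of the T1 window precedes the intervention because training starts late.* The article does not state the lag between baseline and training. That is a separate question, and a 9-month window would not settle it.

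**Conclusion.** The point holds for the 9-month comparison of criminal victimization. A quarter of the T1 window predates baseline, which follows from the stated recall and interview times alone. The attenuation to 0.25 + 0.75R further assumes a constant event rate, equal rates in the arms before baseline, and an effect that starts at baseline. The factor of about 1.4 to 1.6 in clients also rests on the assumed control risks and effects, with clustering ignored. The overlap of months 6 to 9 is a lesser problem, confined to the time course and the correlation between visits. The comparison at 18 months is not diluted. The error works towards missing an early effect and does not by itself create a false one. It deserves correction because it affects a planned comparison on a primary outcome and the remedy is cheap.

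**What to change.** Record the month of each reported incident, if the incident details do not already include it. Define criminal victimization at T0, T1 and T2 as incidents in the 9 months before the interview. The follow-up windows then become 0 to 9 and 9 to 18, with no pre-baseline time and no overlap. Report the 12-month figure descriptively, for comparison with national data.

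If the questionnaire cannot change, state that T2 is the only confirmatory time point for criminal victimization and that T1 is descriptive.

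The cost is one date item per incident, or one sentence in the analysis plan. The downside of the first option is fewer events per window and a primary definition less directly comparable with 12-month figures. The ratios under the working already include that loss of events at T1, and the shorter window still comes out ahead there.

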#### Secondary outcome measures

The following secondary outcome measures will be used to gain more insight into the effects of the Victoria intervention.*Acknowledgement of adversities* related to societal participation is assessed through a self-report questionnaire developed for this study.*Knowledge on rehabilitation and adversities* will be measured through questions for MHP on the domains and phases of the BPR, and through questions on recent conversations about adversities. These questions are also developed for this study.*Self-efficacy* in mental health-related beliefs is measured through the Mental Health Confidence Scale (MHCS) [48], with a 6-point Likert scale, ranging from ‘totally no confidence’ to ‘full confidence’. Cronbach’s alpha for the total scale is 0.93 [49].To measure the *quality of life* the Manchester Short Assessment of Quality of Life (MANSA) is used [50, 51]. The MANSA has good internal consistency (α = 0.72) and is highly correlated (*r* = > 0.83 for each domain) with the Lancashire Quality of Life Profile (LQLP) [50]. The scale consists of 12 questions with a 7-point Likert scale ranging from ‘couldn’t be worse’ to couldn’t be better’ and 4 questions that are answered with yes/no.*General psycho-social functioning* is measured through the Health of the Nation Outcome Scale (HoNOS), a scale that is standard in MHC in the UK [52]. The MHP scores each item on a scale from 0 to 4. The intra class correlation coefficient is 0.92, Cronbach’s alpha is 0.78 and it correlates well with other scales [53]. Moreover, the HoNOS is sensitive to measure change in people with SMI.

#### Additional and control measures

The following measures include instruments that are possible confounding, mediating or control variables.*Socio-demographic characteristics* will be gathered at the start of the interview, including: age, gender, date of birth, number of children, marital status, nationality, education, living situation, income, and number of years in MHC.*Current diagnosis* is gathered from the questionnaire for the MHP.*Social Support* will be derived from the Inventory of Social Reliance (ISR) [54]. It consists of 11 items on emotional and practical support on a 4-point scale ranging from ‘almost never’ to ‘almost always’. The ISR is a frequently used questionnaire for people with SMI and has good psychometric properties [55].*Neighborhood nuisance* is measured through Sections 1 and 2 of the Safety Monitor (see primary outcome measures for more information). These sections contain 9 questions about the experienced safety and contentment in and about their neighborhood.*Perpetration* is assessed with the Safety Monitor. For the same criminal victimization incidents the participants are asked whether they were a perpetrator ever in their life, and if yes, also in the last year.*FACT fidelity* is assessed through the fidelity scores from the CCAF, the Dutch organization that certifies F-ACT teams. The fidelity score is a mean score on 60 items that ranges from 0 to 5, where 0 means ‘no certificate’ and 5 means ‘optimal implementation’.*Adherence to rehabilitation principles* is measured through a sample of the treatment plans of the clients that participate. This treatment plan consists of agreements, goals and wishes on several life domains for the following year.

### RCT analyses

#### Sample size

Sample size is calculated using the model of Twisk [56]. This model is suitable for multiple measurements over time, but can also be used for cluster randomization. With the ratio of the number of subjects in the compared groups being 1 (*r*), a correlation coefficient of the repeated measurements of 0.20 (ρ), a conservative difference between the groups in the mean value of social functioning of 0.25 (*v*), and a power of 1-β = 0.80, the number of participants needed is 151 for each condition at T2 measurement (α = 0.05, two-tailed). Taking into account an attrition rate of 15% for loss due to follow-up or consent withdrawal, 173 participants per condition need to be recruited to achieve the required power.$$ N=\frac{Z\left(1-\alpha /2\right)+Z\left(1-\beta \right)\ 2\ \sigma 2\left(r+1\right)\left[1+\left(T-1\right)\rho \right]}{v2r\ T} $$

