#### Randomization and blinding

The participating teams will be randomly allocated to either the experimental or control condition by an independent senior researcher at Tilburg University, stratified by mental health organization. Cluster randomization was chosen as individual randomization would mean reassigning clients from their regular case managers and was therefore considered to be ethically undesirable. Moreover, cluster randomization reduces risks of contamination between the intervention and control group, as the intervention method is team based. We will monitor staff changes as well as clients switching teams to correct for in statistical analyses.

Due to the nature of the intervention, both the MHP and researchers cannot be unaware of the allocation to the conditions, but they are strongly advised not to disclose to the participating clients whether they receive care from an experimental or control team.

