## Discussion

Outpatients with SMI experience high rates of victimization, discrimination and stigmatization [11–17]. These adversities are important barriers to rehabilitation and societal participation [21]. This study is the first to evaluate an intervention aiming at recognition of victimization and other adversities, that also targets outpatients’ insight and coping skills with regard to possible risks to ensure safe societal participation. The aim of this first trial on the Victoria intervention is to gain insight into the implementation process and effectiveness of the Victoria intervention in reducing victimization (among other adversities) and increasing societal participation, on both the team level and the client level.

A major strength of this study will be the large sample size of outpatients with SMI, leading to sufficient power, which is often a problem in similar trials [59]. Only clients that are unable to fill out the questionnaire during the inclusion period of 6 months, due to insufficient understanding of the Dutch language, prolonged clinical admission, or severe symptomatology, will be excluded from the study. This, as well as the participation of multiple mental health centers, enhances generalizability of results.

This is, to our knowledge, the first study to address victimization and other adversities as a barrier for societal participation. In relation to this, we incorporated a broad range of outcome measures. Many previous studies on victimization only take into account clinical outcome measures or socio-demographic variables such as living situation [13, 14]. Although some studies include the influence of victimization on, for example, quality of life, this study includes a broad range of social outcome measures, such as social functioning and social support. These outcome measures are likely to be influenced by victimization or other adversities in the social domain [60, 61].

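### The sample size makes no allowance for clustering by F-ACT team, so 151 analysed clients per condition in eight teams do not give the stated 80% power

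*Protocol article*

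**What the plan says.** The unit of allocation is the team. Under Randomization and blinding: "The participating teams will be randomly allocated to either the experimental or control condition", stratified by organisation. The Design section gives eight teams in total.

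The Sample size section uses a published repeated-measures formula and says of it: "This model is suitable for multiple measurements over time, but can also be used for cluster randomization". Its stated inputs are:

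- allocation: "With the ratio of the number of subjects in the compared groups being 1"
- correlation: "a correlation coefficient of the repeated measurements of 0.20"
- difference: "a conservative difference between the groups in the mean value of social functioning of 0.25"
- "a power of 1-β = 0.80" and "α = 0.05, two-tailed"

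The result is 151 per condition at T2, raised to 173 for attrition. The Discussion then states: "A major strength of this study will be the large sample size of outpatients with SMI, leading to sufficient power".

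**The concern.** In a cluster-randomised trial the variance of the arm difference includes a between-team component. That component shrinks with the number of teams, not with the number of clients. The formula can deal with repeated measurements or with clustering, according to what its single correlation represents. Here that correlation is expressly the one between repeated measurements on the same client, so nothing in the calculation represents teams.

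A reader of the Sample size section would conclude that clustering had been dealt with, and the Discussion presents power as a strength. If the trial finds no difference, the result would be read as evidence against the intervention from an adequately powered study. The design may have had little better than an even chance, or less, of detecting the difference it was planned for.

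**Working it through.** **Inputs from the article.** Two-sided alpha 0.05, power 0.80, v = 0.25, r = 1, ρ = 0.20, eight teams, 151 analysed per condition.

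**Inputs I assume.** σ = 1 (so v is in SD units) and T = 2 follow-ups; neither is stated in the Sample size section, but together they reproduce 151. Four teams of equal size per arm, inferred from eight teams and r = 1. Team ICC 0.01 to 0.05; the article gives none.

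**Step 1: reproduce the stated figure.** With exponents restored (their loss in the printed formula is not counted as an error):

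N = (z₁₋α/₂ + z₁₋β)² σ² (r+1) [1 + (T−1)ρ] / (v² r T)

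(1.960 + 0.842)² = 7.849. For T = 2: 7.849 × 2 × 1.2 / (0.0625 × 2) = 150.7, i.e. 151. T = 1 gives 251.2 and T = 3 gives 117.2, so only T = 2 matches.

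**Step 2: could 0.20 be the within-team correlation?** Team size would be 151/4 = 37.75. Using that as T: 7.849 × 2 × (1 + 36.75 × 0.20) / (0.0625 × 37.75) = 55.6, i.e. 56 teams per arm. So 151 did not come from a clustered use of the formula.

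**Step 3: power without clustering.** The mean of two follow-ups has variance (1 + 0.20)/2 = 0.6. SE of the difference = √(2 × 0.6/151) = 0.089, and power = Φ(0.25/0.089 − 1.96) = 80%.

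**Step 4: add the teams, in two ways.**

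- *Simple design effect:* Var = (2 × 0.6/151) × [1 + (37.75 − 1) × ICC].
- *Team effect constant over both follow-ups:* Var = 2 × [ICC/4 + (0.6 − ICC)/151].

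Power is given with a normal reference and with a noncentral t on 6 df (8 teams − 2).

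| ICC | Design effect | Power, normal / 6 df | SE, constant team effect | Power, normal / 6 df |
|---|---|---|---|---|
| 0 | 1.00 | 80% / 65% | 0.089 | 80% / 65% |
| 0.01 | 1.37 | 67% / 52% | 0.113 | 60% / 46% |
| 0.02 | 1.73 | 57% / 43% | 0.133 | 47% / 35% |
| 0.05 | 2.84 | 38% / 29% | 0.180 | 28.5% / 22% |

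At an ICC of only 0.005, normal-reference power is 73% (simple) or 69% (constant).

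**Step 5: can more clients in the same eight teams repair it?** With unlimited clients per team the variance tends to 2 × 0.6 × ICC/4 (simple) or 2 × ICC/4 (constant). With a normal reference, 80% power is then attainable only if ICC is below 4/150.7 = 0.027 (simple) or 0.6 × 4/150.7 = 0.016 (constant). On 6 df the limits are 0.018 and 0.011. At ICC 0.02 under the constant model, unlimited clients give 70% (normal) or 55% (6 df).

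**Step 6: minimum detectable difference at 151 per arm.** With a constant team effect and a normal reference it is 2.802 × SE: about 0.32, 0.37 and 0.50 SD at ICC 0.01, 0.02 and 0.05, against the planned 0.25.

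**The case against.** The strongest reply is that these figures are pessimistic.

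- **Baseline.** The primary outcomes are measured at T0 and the planned model is longitudinal. If team effects are stable, baseline data absorb much of them. A generalised least squares analysis using T0, with a common baseline mean and a team effect, gives 72%, 66% and 60% at ICC 0.01, 0.02 and 0.05 (57%, 52% and 46% on 6 df). This stands as a reason to show a range. It does not rescue the claim: the stated calculation uses no baseline, and power remains below 80%.
- **More clients.** The caseload exceeds 1500, about 750 per arm. At ICC 0.01 (normal reference), 80% needs about 239 analysed per arm under the simple design effect or 398 under the constant model. At ICC 0.02 with the simple design effect, 750 per arm would give 82%. So more clients can help when the ICC is small, within the limits in Step 5. How many would be eligible and consent is unknown, and the article plans 151.
- **Degrees of freedom.** The 6-df reference is my choice; the article specifies none. The normal-reference figures do not depend on it and still fall short. All the power figures presuppose an analysis that respects teams. An analysis that ignored them would risk inflated type I error, which is no answer to lost power.
- **The cited formula may well serve for clusters.** Agreed, but that use was not made here.

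Nor is this a detail the article leaves to a fuller document: it prints the formula, inputs and result, and 151 follows from them with no team term.

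**Conclusion.** The concern holds. The figure of 151 per condition is an individual-randomisation sample size for the mean of two follow-ups, and the 80% power belongs to that design rather than to one with eight randomised teams. Across ICCs of 0.01 to 0.05, with a normal reference, power is 67% to 38% under the simple design effect, 60% to 28.5% with a constant team effect, and 72% to 60% in the most favourable baseline-adjusted case. With 6 team-level degrees of freedom every one of these is lower. The exact shortfall rests on the assumed ICC, four equal teams per arm, σ = 1 and T = 2. The direction does not: every non-zero ICC examined puts power below 80%. This needs correcting because the article asserts a property that the design does not have.

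**What to change.** Keep the planned number of clients and rewrite the power paragraph:

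1. State that 151 per condition allows for repeated measurements only.
2. Report power for eight teams at the expected team size, over an explicit ICC range such as 0.01 to 0.05 (with a source if one is available), using a t reference with team-level degrees of freedom. If the analysis will use T0, say how, and give the baseline-adjusted power as well.
3. Remove the sentence on cluster randomisation, or qualify it to say that the formula was not applied in that way here.
4. In the Discussion, replace the claim of sufficient power with the restated power or the minimum detectable difference. If that is what remains, describe the trial as giving a first estimate of effect.

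The cost is rewording one section and one Discussion sentence, and a less favourable stated power. No additional clients or teams are required.
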